**Primary endpoints:**
1. 30% reduction in attack frequency with TENS and ONS
2. Safety in ONS and TENS treatment

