**Secondary endpoints**
1. Participant’s assessment of treatment effect evaluated by PGIC-score
2. Treatment efficacy of burst versus tonic ONS as a preventive treatment for chronic cluster headache
3. Feasibility of TENS as a predictor for the outcome of ONS treatment
4. 30% reduction in pain intensity
5. Quality of life as evaluated with the EuroQoL-5D questionnaire
6. Reduction in background headache
7. Self-reported sleep quality
8. Symptoms of anxiety and depression as evaluated by HADS

*TENS* Transcutaneous electrical nerve stimulation, *ONS* Occipital nerve stimulation, *PGIC* Patient's global impression of change, *HADS* Hospital anxiety, and depression scale, *EuroQoL-5D* European Quality of Life – 5 Dimensions

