### Sample size

Based on our previous experience with ONS treatment [26], we estimate that 50% of the participants who receive active treatment with burst ONS will reach the primary endpoint of a 30% reduction in attack frequency. A blinded trial with burst ONS and placebo has to our knowledge not been carried out earlier, but we hypothesize that no more than 10% in the placebo group will meet the primary endpoint [35]. The sample size is calculated using Fisher’s Exact test based on the above-mentioned assumptions and with 80% power (two-tailed) and a α = 0.05, a total of 40 participants (20 in each allocation group) are needed to be enrolled in the study and an ONS-system implanted.

Each enrolled participant contributes their data regardless of whether they complete the project or not. In case of participants excluded after enrollment, the reason for exclusion will be described.

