### Statistical analysis

Statistical analysis will be conducted by the principal investigator and a statistician blinded for treatment allocation only after follow-up for all participants is completed. No interim analysis will be performed.

Characteristics of the patients will be presented using descriptive statistics to assess if balanced groups were obtained after randomization. The primary analysis will be conducted according to the intention-to-treat principle to avoid introducing bias. In a secondary analysis, a per-protocol analysis will be performed.

The primary outcome is a 30% reduction in attack frequency with TENS and ONS treatment compared to baseline. Relative change in attack frequency (in percent) will be analyzed using the Wilcoxon signed-rank test for paired variables, comparing the baseline data with data from the TENS trial and the trial with burst and tonic ONS, respectively. Because the changes in attack frequency are expectedly skewed [23], a non-parametric test will be applied. In cases with a minimum 30% reduction in attack frequency, sub-analyses will be made to group the treatment responders after relevant cutoffs.

Analysis of the secondary outcomes will be conducted according to the same principle, comparing data from each of the trial phases to baseline using a parametric or non-parametric test for paired variables, depending on the data distribution.

The feasibility of TENS as a predictor for ONS outcome will be evaluated by determining the sensitivity and specificity and calculating the predictive values.

Statistical data analysis will be performed using Stata 17.0 (StataCorp, College Station, USA-TX).

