## Discussion

The effect of ONS on CCH has primarily been evaluated in case series and uncontrolled open-label studies [14–19], aside from a single large dose–response RCT [23]. In the 2023 European Academy of Neurology Guidelines on Cluster Headache [38] there is no recommendation for ONS due to the very low level of evidence. To our knowledge, the study presented here is the first randomized, blinded, placebo-controlled trial on ONS treatment for CCH; when completed, it should constitute a significant contribution to the evidence in the field.

Although little is known about burst stimulation for ONS, there are indications that this type of stimulation also has a preventive treatment effect in CCH patients. Because the participants do not perceive any sensation of stimulation, it enables the conduction of a blinded trial with burst ONS as the active comparator to an inactive placebo treatment.

Burst stimulation was introduced in 2010 and later marketed by neuromodulation device manufacturer Abbott as BurstDR. Subsequently, other manufacturers of neuromodulation systems have developed similar waveforms marketed under other burst labels. A difference in mechanism of action has been claimed [39], however, in this study we do not distinguish between the different variations of the burst waveforms.

The study design allows a comparison between burst ONS and placebo and enables a head-to-head comparison of the efficacy of burst and tonic ONS. In addition, by comparing the effect of treatment with TENS and tonic ONS, respectively, it is possible to evaluate whether the effect of TENS can be used as a feasible preoperative screening tool for ONS outcomes and can be used to select the most eligible candidates for implantation.

There is no official consensus about optimal stimulation settings in ONS for CCH. The study will provide important information about the efficacy of burst ONS and explore whether the addition of this stimulation paradigm might help improve future stimulation protocols.

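### TENS as a predictor of ONS outcome is assessed only with yes/no measures in at most 40 people; adding a full-scale analysis of data already collected would be a cheap improvement to this secondary endpoint

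*Protocol article*

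**What the plan says.** Table 4 of the protocol article lists as a secondary endpoint: "Feasibility of TENS as a predictor for the outcome of ONS treatment". The Statistical analysis section gives the method in one sentence: "The feasibility of TENS as a predictor for ONS outcome will be evaluated by determining the sensitivity and specificity and calculating the predictive values". No correlation, regression or ROC analysis is named for this question.

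The ONS outcome that TENS is set against is tonic stimulation. The Discussion describes the evaluation as made "by comparing the effect of treatment with TENS and tonic ONS, respectively". All participants pass through both phases, so up to 40 pairs can exist.

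The only numerical responder threshold for attacks is the primary endpoint, "30% reduction in attack frequency with TENS and ONS". Beside it, the Statistical analysis section says that "sub-analyses will be made to group the treatment responders after relevant cutoffs". Neither is tied to the predictor analysis. The same section keeps the full scale for efficacy: "Relative change in attack frequency (in percent) will be analyzed using the Wilcoxon signed-rank test for paired variables".

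**The concern.** Sensitivity, specificity and predictive values need a yes/no TENS result and a yes/no ONS result. Both come from weekly attack counts (Headache registration section), so the trial will hold a percent change for each participant in each phase. The article uses that scale for efficacy and drops it for prediction. A participant with a 31% reduction under TENS is then treated like one with a 90% reduction, and unlike one with a 29% reduction, if the 30% threshold is the cut. Nothing in the article suggests that the efficacy threshold is also the best screening threshold.

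At stake is one of the declared purposes of the study: whether a non-invasive test can help decide who receives an implant. If the only results are four proportions from a small table, a moderate screening signal may be too imprecise to recognise.

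**Working it through.** **1. The plan's own figure.** No size, power or precision is given for the predictor question. The total comes from burst against placebo: "a total of 40 participants (20 in each allocation group) are needed to be enrolled in the study". With 50% against 10%, two-sided alpha 0.05 and 80% power, the pooled formula gives

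n = [1.96·√(2·0.3·0.7) + 0.842·√(0.5·0.5 + 0.1·0.9)]² / 0.4² = (1.270 + 0.491)² / 0.16 ≈ 19.4, so 20 per group and 40 in total.

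The total reproduces by that formula, but it was not set for this endpoint. (The Fisher test that the Sample size section names has about 74% power at 20 per group. That is a separate matter.)

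**2. Precision of the planned measures.** Exact (Clopper-Pearson) 95% intervals need no assumed correlation:

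- 20 ONS responders of 40 (50%, the plan's figure for burst): 13/20 = 65%, CI 41% to 85%; 16/20 = 80%, CI 56% to 94%.
- About two-thirds responders, as the Background cites for open-label ONS at a 50% reduction: 0.67 × 40 ≈ 27 responders and 13 non-responders. An observed sensitivity of 21/27 = 78% has a CI of 58% to 91%. An observed specificity of 10/13 = 77% has a CI of 46% to 95%.

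**3. Information lost by cutting both responses.** Assumptions, none of them in the article: bivariate normal changes with correlation rho; 30% or 50% TENS responders; 50% or 67% tonic ONS responders; n = 40; two-sided 0.05. There were 4,000 to 10,000 simulated trials per setting, so the Monte Carlo standard error is at most √(0.25/4000) ≈ 0.8 points. The table gives the share of trials that detect the association, as the approximate range over the four combinations of responder rates:

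| rho | 2x2, Fisher | 2x2, chi-square | TENS continuous, ONS yes/no (ROC area, Mann-Whitney) | Both continuous (Spearman) |
|---|---|---|---|---|
| 0.4 | 20–29% | 28–37% | 47–52% | 67–70% |
| 0.5 | 33–46% | 42–57% | 68–73% | 88–89% |
| 0.6 | 49–65% | 59–75% | 86–89% | 97–98% |
| 0.7 | 66–84% | 75–90% | 96–98% | about 100% |

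With 32 pairs (an assumed 20% loss) and rho 0.5, Fisher gives 25–39% and Spearman 79–81%.

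**4. What these correlations mean for screening.** With 50/50 splits, sensitivity = specificity = 0.5 + arcsin(rho)/π. This is 63% at rho 0.4, 67% at 0.5 and 75% at 0.7.

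**The case against.** The strongest reply is that the article describes estimation, not testing. It names Fisher's test only for the burst-against-placebo sample size, and rho appears nowhere. A reader might infer from the table that the planned analysis would miss most real associations and report a useful signal as absent. The article does not support that: it contains no test that could miss anything. Even as a measure of information, the statement fails from rho of about 0.6, where the 2x2 table detects roughly half to two-thirds. Part of the gap is also Fisher's conservatism rather than the cutting, as the chi-square column shows. This part of the reply stands.

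Second, implanting is a yes/no decision, and sensitivity, specificity and predictive values are the usual measures for it. At rho 0.4 to 0.5 they are only 63–67% with even splits, so many of the associations at issue would be weak guides to surgery. A reader might conclude that these measures are wrong or should be demoted. They should not be.

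Third, the article fixes no single TENS cut, so an ROC curve, which is sensitivity and specificity over all cuts, is compatible with its sentence. A reader who infers that the 30% threshold is the planned screening cut goes beyond the text. Cutoffs and intervals may well stand in a full protocol or SAP that is not shown, and their absence here is not the point.

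Fourth, the 41% to 85% interval comes from the sample size. A full-scale analysis does not narrow it.

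What remains is that the stated choice rests on dichotomised measures alone, while better data for the same question are already collected.

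**Conclusion.** The point holds as a cheap improvement to a secondary endpoint. The stated measures are appropriate but imprecise, and relying on them alone discards much of the information in at most 40 pairs. The imprecision in step 2 follows from the numbers of responders and non-responders alone, given the responder rates shown. The size of the information loss rests on the assumed normal model, rho and responder rates. At rho 0.4 to 0.5 detection is about 20–46% with both responses cut, 47–73% with TENS kept continuous and 67–89% with both continuous. The gap narrows for strong association. Nothing in the article is false or contradictory on this point, and the primary endpoints are not affected.

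**What to change.** Keep sensitivity, specificity and predictive values as the clinical decision summary, with exact 95% CIs, at a TENS cut and an ONS response definition fixed before analysis. Add two results:

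- **(a)** the ROC area with 95% CI for continuous percent change under TENS against tonic ONS response;
- **(b)** one full-scale association that tolerates participants with zero attacks in a phase. This can be the Spearman correlation with 95% CI between percent change under TENS and under tonic ONS, or a negative binomial model of tonic-phase attack counts on TENS-phase attack rate, adjusted for baseline rate.

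A regression on log attack rates is not suitable as it stands, because the log is undefined for a zero count. Both percent changes share the same four-week baseline, so part of any association between them, in the 2x2 table as well, reflects that common denominator. The count model is less exposed to this. The power figures above are for the rank methods; the gain from the count model was not evaluated.

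The cost is a few lines of analysis-plan wording and a little more analysis work, with no new data or visits. The downside is a coefficient that clinicians read less directly, which is one more reason to keep the 2x2 summary beside it.

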**Methods:**

An investigator-initiated, double-blinded, randomized, placebo-controlled trial is conducted, including 40 patients with CCH. Eligible patients complete a trial with the following elements: I) four weeks of baseline observation, II) 12 weeks of transcutaneous electrical nerve stimulation (TENS) of the occipital nerves, III) implantation of a full ONS system followed by 2 week grace period, IV) 12 weeks of blinded trial with 1:1 randomization to either placebo (deactivated ONS system) or burst (paresthesia-free) stimulation, and V) 12 weeks of tonic stimulation.

The primary outcomes are the reduction in headache attack frequency with TENS and ONS and treatment safety. Secondary outcomes are treatment efficacy of burst versus tonic ONS, the feasibility of TENS as a predictor for ONS outcome, reduction in headache pain intensity (numeric rating scale), reduction in background headache, the patient’s impression of change (PGIC), health-related quality of life (EuroQoL-5D), self-reported sleep quality, and symptoms of anxiety and depression (Hospital Anxiety and Depression Scale, HADS).

Data on headache attack characteristics are registered weekly. Data on patient-reported outcomes are assessed after each trial phase.

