**Discussion:**

The study design allows a comparison between burst ONS and placebo in refractory CCH and enables a comparison of the efficacy of burst and tonic ONS. It will provide information about the effect of burst ONS and explore whether the addition of this stimulation paradigm may improve stimulation protocols.

TENS is evaluated as a feasible preoperative screening tool for ONS outcomes by comparing the effect of attack prevention of TENS and tonic ONS.

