**Fig. 2 Fig2:**
[figure not shown]
Outcome parameters in correlation to trial phases and study visits. TENS, transcutaneous electrical nerve stimulation. ONS, occipital nerve stimulation. PGIC, patient's global impression of change. HADS, hospital anxiety and depression scale. EuroQoL-5D, European Quality of Life – 5 Dimensions

All questionnaires are electronic and are entered via a personal link sent automatically by e-mail. If the headache registrations and questionnaires are not completed within 24 h, an e-mail reminder is generated.

The data collected during each trial phase will be compared to the baseline and analyzed in order to evaluate the study endpoints listed in Table 4.

**Table 4 Tab4:** Study endpoints

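### Measuring TENS response and tonic ONS response from the same four-week baseline biases the accuracy of TENS as a predictor upward

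*Protocol article*

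**What the plan says.** The Abstract (Methods) sets out "four weeks of baseline observation", then "12 weeks of transcutaneous electrical nerve stimulation (TENS) of the occipital nerves", and as the last phase "12 weeks of tonic stimulation". Under Outcome measures, below Fig. 2, the protocol says "The data collected during each trial phase will be compared to the baseline and analyzed in order to evaluate the study endpoints". The Statistical analysis section adds: "The primary outcome is a 30% reduction in attack frequency with TENS and ONS treatment compared to baseline".

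On prediction, the same section says "The feasibility of TENS as a predictor for ONS outcome will be evaluated by determining the sensitivity and specificity and calculating the predictive values". The Abstract (Discussion) names the target: TENS is to be evaluated "by comparing the effect of attack prevention of TENS and tonic ONS". The Discussion section gives the purpose, namely to learn whether the TENS effect "can be used to select the most eligible candidates for implantation".

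The protocol describes no second baseline, no untreated period just before tonic ONS, and no allowance for the common reference. It does not say in so many words that the 30% cut defines both sides of the predictor table. That is the only attack-frequency threshold it gives, however, and any other cut on percent change from baseline would keep the same denominator.

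**The concern.** A participant whose four baseline weeks happened to be bad will appear to improve on TENS and again on tonic ONS. One whose baseline weeks happened to be good will appear to improve on neither. The 2x2 table counts both as agreement. Part of the measured accuracy therefore comes from noise in the shared denominator, and the planned statistics cannot separate that part from real prediction.

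At stake is the reading of secondary endpoint 3 (Table 4). The protocol looks ahead to using TENS to choose candidates for implantation, so inflated accuracy would bear on advice to later patients.

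**Working it through.** The protocol states no expected accuracy and no sample size for this analysis, so there is no figure of its own to reproduce.

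**Inputs from the protocol.** Baseline 4 weeks; TENS 12 weeks; tonic ONS 12 weeks; response = at least 30% fall from baseline; at least 15 attacks per month at entry; 40 participants, 20 per arm; placebo response no more than 10% (Sample size).

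**Assumptions, not in the protocol.** Mean attack rate, week-to-week or phase-to-phase variation, and the spread of true effects. Each is varied below.

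**Step 1: the mechanism.** Let σ² be the weekly variance of the log attack rate, independent between weeks, with neither treatment having any effect. Then log(TENS/baseline) and log(ONS/baseline) share the baseline term:

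- covariance = σ²/4
- variance of each = σ²/4 + σ²/12
- correlation = (1/4)/(1/4 + 1/12) = 0.75

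True effects that vary between patients dilute this. Take 5 attacks per week, weekly CV 0.3, and independent effects with log-SD 0.4 (TENS) and 0.6 (ONS). Then σ² ≈ 1/5 + 0.3² = 0.29, the covariance is 0.0725, and the variances are 0.0967 + 0.16 = 0.2567 and 0.0967 + 0.36 = 0.4567. The correlation is 0.0725/√(0.2567 × 0.4567) = 0.21; simulation gives 0.23. The true value is 0.

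**Step 2: weekly-noise simulation.** Mean 20 attacks per 4 weeks; median reduction 10% (TENS) and 30% (ONS), drawn independently. A test without information has Youden 0 and a positive predictive value (PPV) equal to the ONS response rate.

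| Weekly CV | Baseline | Sens. | Spec. | Youden | PPV | ONS response |
|---|---|---|---|---|---|---|
| 0 | shared | 0.335 | 0.752 | 0.087 | 0.563 | 0.488 |
| 0 | split | 0.299 | 0.702 | 0.001 | 0.479 | 0.479 |
| 0.3 | shared | 0.357 | 0.758 | 0.115 | 0.582 | 0.485 |
| 0.3 | split | 0.305 | 0.692 | −0.003 | 0.467 | 0.470 |
| 1.0 | shared | 0.480 | 0.789 | 0.269 | 0.661 | 0.461 |
| 1.0 | split | 0.336 | 0.662 | −0.001 | 0.441 | 0.442 |

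Split means weeks 1-2 are the reference for TENS and weeks 3-4 for ONS. At 60 attacks per 4 weeks the shared-baseline Youden is 0.039, 0.075 and 0.262 for the same three CVs. With TENS inert and ONS response near 50%, it runs from 0.01 to 0.28. With no effect of either treatment it is 0.29 to 0.47.

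**Step 3: phase-level noise.** Here the attack rate drifts between phases with log-SD 0 to 0.4. Mean rate is about 7 per week; log effects are −0.15 (SD 0.2) for TENS and −0.5 (SD 0.5) for tonic ONS, independent. Youden is 0.10 to 0.24 with the shared baseline and 0.00 with an independent one.

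**Step 4: calibration to the protocol.** With no placebo effect, the device-off response rate in the Step 3 model is about 4%, 8%, 15%, 22% and 28% at log-SD 0, 0.1, 0.2, 0.3 and 0.4. Only log-SD up to about 0.1 agrees with the 10% ceiling. In that range, at mean rates of 5 to 12 per week, Youden is about 0.08 to 0.14, and a Fisher test on the table of 40 is significant in about 5 to 11% of trials.

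**Step 5: device off.** In the Step 3 model, TENS response also predicts blinded-phase response in the placebo arm, with sensitivity about 0.6, specificity 0.72 to 0.79 and Youden 0.33 to 0.41. There is no stimulation there to predict.

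**Step 6: limits of splitting.** If the fluctuation lasts through all four weeks, both halves carry it. Youden of about 0.07 to 0.19 then remains at log-SD 0.2 to 0.4.

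**The case against.** **Size.** The larger values need more variability than the protocol's own 10% placebo hypothesis allows. This stands. The 10% is a hypothesis and not data, but it is the only anchor in the document, so 0.08 to 0.14 is the range to quote first.

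**Certainty and consequence.** A reader might infer that TENS will look like a valid screening test whatever the truth. The documents do not support that. Sensitivity of 0.28 to 0.48 with Youden of 0.10 to 0.24 is poor on its face. In Step 2 the standard error of Youden at 40 participants is about 0.14 to 0.15, as large as the calibrated bias. The endpoint is secondary, the aim is framed as exploratory, and every participant is implanted whatever the TENS result, so nobody in the trial is refused surgery. These points limit the severity but leave the bias in place.

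**Placebo responders.** It is tempting to add that both phases are open-label with felt paresthesia, so non-specific responders inflate agreement. That is not a fault of this analysis. The stated question is whether TENS predicts ONS outcome, and a patient who responds non-specifically to both is correctly predicted. Whether TENS predicts specific ONS benefit is a different question.

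**Detail left elsewhere.** Confidence intervals and by-arm tables may sit in a fuller plan, and their absence from an article is no finding. The shared reference is different, because the article fixes it.

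**Conclusion.** The point holds as an expected upward bias of certain direction and uncertain size. In the simulations with independent true effects, the mean Youden index was above 0 in every shared-baseline setting and about 0 with an independent baseline. The calibrated range of 0.08 to 0.14 rests on assumed attack rates, assumed spread of effects, and the 10% placebo hypothesis taken as a bound on natural fluctuation. Strong swings between phases bring it to about 0.25. Low noise with TENS inert brings it to about 0.01. It would be higher still if neither treatment worked.

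This is worth correcting before analysis because the correction is cheap. It does not touch the randomised comparison.

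**What to change.** 1. Keep the tonic ONS table, and add a sensitivity analysis with baseline weeks 1-2 as the reference for TENS response and weeks 3-4 for ONS response. State that this removes the bias only for noise that does not persist across the four weeks. State also that two-week references attenuate a true association: with perfectly correlated effects, Youden falls from about 0.38 to 0.26 at log-SD 0 to 0.1, which combines lost bias and attenuation.
2. As an exploratory analysis, tabulate TENS response against blinded-phase response separately in the burst and placebo arms, and estimate the TENS-by-arm interaction on continuous log attack rate. The device-off table shows how much apparent prediction arises without stimulation. It should not be subtracted from the tonic table, because the artefact on the responder scale differs between settings (0.33 to 0.41 with the device off, 0.10 to 0.24 for tonic ONS in the same model). The interaction on the log scale is the cleaner contrast, since baseline error affects both randomised arms alike.
3. Do not report the tonic table alone as validating TENS as a screening test for implantation.

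**Cost.** Extra analysis only; the weekly counts and the device-off arm already exist. The arm comparison concerns burst and not tonic ONS, and it is imprecise. At 10% response, 20 placebo participants give 20 × 0.10 = 2 expected responders, and none at all with probability 0.9^20 = 12%. It should inform interpretation and not serve as a pass/fail condition.
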